### Analysis methods

The distribution of continuous variables will be assessed via visual inspection of histograms, Q‒Q plots, and normality tests such as D’Agostino‒Pearson tests. Variables with a normal distribution will be shown as the means and SDs, and those without a Gaussian distribution will be presented as medians and interquartile ranges (IQRs). For categorical variables, counts and percentages will be calculated whenever appropriate. This is shown in tables 1 and 2 (dummy tables), and tables 2S to 8S (Supplementary Material).

### Statistical software

Analysis will be performed via R version 4.2.3 software.

### Participant flow

#### Screening data

An active daily screening for potentially eligible patients is performed across all participating ICUs. Patients meeting the septic shock criteria upon admission or meeting these criteria during their ICU stay, as defined by the Sepsis-3 consensus will undergo screening.^11^Inclusion or exclusion decisions are communicated to the study coordinating center (SCC) through a designated internet-based tool (form), with reasons for exclusion documented. Centers are required to report included or excluded subjects to the SCC on a weekly basis.

#### Eligibility

Consecutive adult patients (≥ 18 years old) with septic shock admitted to the intensive care unit will be considered eligible. Septic shock is defined as suspected or confirmed infection, hyperlactatemia (≥ 2.0mmol/L) and the need for vasopressors due to refractory hypotension.^6^

The exclusion criteria include a duration of more than 4 hours after the onset of septic shock, anticipated surgery or dialysis procedure during the first 6 hours after septic shock diagnosis, active bleeding, do-not-resuscitate status, child B-C cirrhosis, underlying disease process with a life expectancy < 90 days and/or the attending clinician deems aggressive resuscitation unsuitable, refractory shock (defined as high risk of death within 24 hours), pregnancy, concomitant severe respiratory distress syndrome, and the inability to accurately assess CRT.

Patients deemed eligible may not be randomized in the case of consent denial, logistical reasons, lack of approval to participate from the attending physician (MD), or a delay in the transfer process leading to a loss of the 4-hour inclusion window.

#### Recruitment

Details for the CONSORT flow diagram are presented in figure 2.

**Figure 2 f02:**
[figure not shown]
CONSORT flow.

#### Withdrawal/follow-up

We will document the number of patients whose consent for trial participation is withdrawn either by the patient or his or her legal representative. When consent is withdrawn for trial participation, we nevertheless attempt to obtain consent for the collection and analysis of follow-up data. These cases will also be reported.

#### Baseline patient characteristics

The baseline characteristics recorded during the trial will be presented in table 1 (dummy).

**Table 1 t1:** Patient characteristics at randomization

Characteristic	CRT-P guided resuscitation (n = xxx)	Usual care (n = xxx)
Demographics		
Age (years)	xx (xx – xx)	xx (xx – xx)
Sex		
Men	xx (xx)	xx (xx)
Women	xx (xx)	xx (xx)
Body mass index	xx (xx – xx)	xx (xx – xx)
APACHE II	xx (xx – xx)	xx (xx – xx)
Baseline SOFA score	xx (xx – xx)	xx (xx – xx)
Charlson Comorbidity Index	xx (xx – xx)	xx (xx – xx)
Time from hypotension to antibiotic start (hours)	xx (xx – xx)	xx (xx – xx)
Time from meeting entry criteria to randomization (hours)	xx (xx – xx)	xx (xx – xx)
Comorbidities		
Hypertension	xx (xx)	xx (xx)
Diabetes	xx (xx)	xx (xx)
Chronic obstructive pulmonary disease	xx (xx)	xx (xx)
Chronic renal disease	xx (xx)	xx (xx)
Hematological cancer	xx (xx)	xx (xx)
Nonhematological Cancer	xx (xx)	xx (xx)
Immunosuppression	xx (xx)	xx (xx)
Liver disease	xx (xx)	xx (xx)
Heart failure	xx (xx)	xx (xx)
Coronary artery disease	xx (xx)	xx (xx)
Source of infection		
Abdominal	xx (xx)	xx (xx)
Lung	xx (xx)	xx (xx)
Urinary tract	xx (xx)	xx (xx)
Soft tissues	xx (xx)	xx (xx)
Primary bacteremia	xx (xx)	xx (xx)
Other	xx (xx)	xx (xx)
Unknown	xx (xx)	xx (xx)
Characteristics at randomization		
Resuscitation fluids at randomization (mL)	xx (xx – xx)	xx (xx – xx)
Supplemental oxygen	xx (xx)	xx (xx)
Mechanical ventilation		
Invasive	xx (xx – xx)	xx (xx – xx)
Noninvasive	xx (xx – xx)	xx (xx – xx)
Lactate > 4.0 mmol/L	xx (xx)	xx (xx)
Lactate level (mmol/L)	xx (xx – xx)	xx (xx – xx)
Mottling score		
Capillary refill time (seconds)	xx (xx – xx)	xx (xx – xx)
Norepinephrine dose* (mcg/kg/minute)	x.xx (x.xx - x.xx)	x.xx (x.xx - x.xx)
Vasopressin use	xx (xx)	xx (xx)
Venous-to-arterial carbon dioxide difference (mmHg)	xx (xx – xx)	xx (xx – xx)
Central venous oxygen saturation	xx (xx – xx)	xx (xx – xx)

CRT-P - Intervention Group; APACHE - Acute Physiology and Chronic Health Evaluation; SOFA - Sequential Organ Failure Assessment. * Expressed as a norepinephrine base.

## Analysis

### Outcome definitions

#### Primary outcome

The primary outcome of the study is a hierarchical composite outcome: (1) all-cause mortality within 28 days, (2) time to cessation of vital support truncated on Day 28, and (3) length of hospital stay truncated on Day 28.

#### Secondary outcomes

The following are the secondary outcomes assessed in a hierarchical fashion: 1) all-cause mortality within 28 days; 2) vital support-free days within 28 days, defined as the number of days between randomization and 28 days after randomization in which the patient is alive and does not require cardiovascular, respiratory, and/or renal support (a value of zero will be assigned to patients who die within 28 days, regardless of their life support status) and 3) length of hospital stay, truncated on Day 28.

#### Tertiary outcomes

The tertiary clinical outcomes are as follows: all-cause mortality within 90 days after randomization, length of hospital stay, length of ICU stay, time to cessation of vasopressor support, time to cessation of mechanical ventilation (MV), time to cessation of renal replacement therapy (RRT), vasopressor support-free days, MV-free days, RRT-free days, variation in Sequential Organ Failure Assessment (SOFA) score, variation in creatinine-based Kidney Disease: Improving Global Outcomes (KDIGO) stage, volume of resuscitation fluids, net fluid balance, evolution of CRT, evolution of lactate levels, evolution of central venous pressure (CVP), evolution of central venous oxygen saturation (ScvO2), and evolution of the central venous to arterial carbon dioxide difference (delta pCO2(v-a)).

## Primary outcome analysis

This outcome will be analyzed via the stratified win ratio method, with treatment used as a fixed effect and the APACHE II score used as a stratifying variable.^12,13^All the patients in the CRT-P group will be compared with all the patients in the Control Group following the hierarchical primary outcome. Thus, in each pair, the comparison will focus first on mortality (1). If only one patient dies, the surviving patients will sum a win. If both patients in a pair die, it will be deemed a tie, leading to no further comparisons for this pair. If both patients survive past 28 days, the analysis will shift to the time to cessation of vital support (2). A win will be assigned to the group containing the patient with the shortest time to cessation of vital support. If the duration (in days) is equal within the pair, then the length of hospital stay (3) will be compared. A win will be counted for the treatment group with the patients having the shortest hospital stay. If the length is identical, it will be marked as a tie.

The win ratio is calculated as:

$$\text{ Win ratio }\frac{\text{ Number of wins in the experimental group }}{\text{ Number of wins in the Control Group }}$$

The bootstrap resampling method will be used to calculate the 95% confidence interval (95%CI) for the win ratio and p value for the hypothesis test and is reported in figure 3 (dummy). The results will be reported as win ratios with 95%CIs and p values. The win ratio is interpreted as follows: in any pair of patients, one treated with the experimental intervention and the other with the control intervention, and as long as there is no tie, the win ratio is the probability that the treated patient will have a better outcome.

**Figure 3 f03:**
[figure not shown]
Primary outcome (win ratio) analysis dummy figure.

Compared with the original analysis approach described by Pocock et al.,^12^our analysis has modifications. In the original analysis, death was assessed as a time-to-event variable, and even if both patients of a pair died, the one who lived longer would win. In our study, we consider death within 28 days as a binary event, and if both patients in a pair die, we consider this a tie. This is based on the assumption that a later death within a 28-day period would not be considered a benefit from patients’ perspectives.

## Secondary outcome analysis

The effect on 28-day all-cause mortality will be assessed with a Cox proportional hazard model adjusted for baseline APACHE II score and presented as hazard ratios with 95%CI, similar to the analysis implemented in the ANDROMEDA SHOCK trial.^14^The effect on vital support-free days within 28 days will be assessed with a cumulative logistic model adjusted for the baseline APACHE II score and presented as odds ratios with 95%CIs. The length of hospital stay, which is truncated on Day 28, will be estimated with generalized linear models adjusted for the APACHE II score using the distribution that best fits the data. The results will be presented in table 2 (dummy). The results of residual and QQ-plot analysis will be published in the supplementary manuscript to increase transparency.

**Table 2 t2:** Outcomes

Characteristic	CRT-P guided resuscitation (n = xxx)	Usual care (n = xxx)	Effect estimate	Effect size (95%CI)	p value
Primary outcome					
Hierarchical composite outcome at 28 days*	xxx / xxx (xx.x)	xxx / xxx (xx.x)	Win ratio	x.xx (x.xx to x.xx)	.xx
Secondary outcomes					
All-cause mortality within 28 days	xxx / xxx (xx.x)	xxx / xxx (xx.x)	Hazard ratio	x.xx (x.xx to x.xx)	.xx
Vital support-free days within 28 days	xx.x (xx.x; xx.x)	xx.x (xx.x; xx.x)	TBD†	x.xx (x.xx to x.xx)	.xx
Length of hospital stay (truncated at 28 days)	xx.x (xx.x; xx.x)	xx.x (xx.x; xx.x)	TBD†	x.xx (x.xx to x.xx)	.xx

CRT-P - Intervention Group; 95%CI - 95% confidence interval; * Composite Hierarchical Outcome: all-cause mortality, then time to cessation of vital support, and length of hospital stay, truncated at 28 days. † A generalized linear model with the distribution that best fits the data will be adjusted; thus, the effect estimate measure will be subsequently defined.

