### Statistical analysis principles

We will report two-sided p values for the primary outcome main analysis. If the experimental group strategy is superior to the Control Group for the primary outcome (p value < 0.05), we will test the treatment effect on the secondary outcomes in a hierarchical fashion at a significance level of 0.05. Ninety-five percent confidence intervals will be presented for all effect estimates. P values will not be presented for tertiary outcomes or other analyses. Owing to the risk of Type I error from numerous comparisons, the results for tertiary outcomes and other analyses should be considered exploratory.

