## Tertiary outcome analysis

All-cause mortality within 90 days will be assessed with a Cox proportional hazard model adjusted for the baseline APACHE II score. The effects on the length of hospital stay, length of ICU stay, time to cessation of vasopressor support, time to cessation of MV, and time to cessation of RRT will be estimated with generalized linear models using the distribution that best fits the data and adjusted for the baseline APACHE II score. Vasopressor support-free days, MV-free days, and RRT-free days will be assessed with a cumulative logistic model adjusted for the baseline APACHE II score.^15,16^Effects on repeated measures of organ dysfunction at 7 days (SOFA), CRT and lactate levels will be analyzed via mixed models with patients as random effects, treatment groups as fixed effects, and treatment‒time interactions while adjusting for the baseline SOFA score. The effect will be presented as the difference between the slopes of the groups or, equivalently, the treatment‒time interaction. The effects on other continuous outcomes, such as length of hospital stay and length of ICU stay, will be calculated with generalized linear models with the distribution that best fits the data. Adjustments for baseline APACHE II score, evolution volume resuscitation fluid, and net fluid balance will also be assessed with generalized linear models with the distribution that best fits the data and no adjustments for baseline covariates. For all continuous outcomes for which we will define the best distribution at the time of statistical analysis, the criteria will involve assessing which distribution best fits the data via residual and QQ-plot analysis, which will be published in the supplementary manuscript to increase transparency.

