## Heterogeneity of treatment effects

We will assess whether treatment varies according to baseline patient characteristics via conventional subgroup analysis and risk modeling.^17^

The effect of the treatment on the primary hierarchical composite outcome will be assessed according to the following subgroups: age (< or ≥ 65 years), APACHE II score (< or ≥ 25 points), SOFA score (< or ≥ 10 points), baseline lactate level (< or ≥ 4mmol/L), baseline CRT (< or ≥ 3 seconds), origin of septic shock (pulmonary, abdominal, urinary, soft tissue *versus* bacteraemia *versus* other), and invasive mechanical ventilation at inclusion.

We will assess the heterogeneity of treatment effects by risk modeling through analysis of the win ratio according to quintiles of APACHE-2 scores.^17^

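### The three formally tested secondary outcomes adjust for APACHE II alone although SOFA, lactate, norepinephrine dose and ventilation at randomisation are collected: an unused gain in power, not an error

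*SAP article*

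**What the plan says.** All three models are in the SAP article, Secondary outcome analysis:

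- Mortality: "The effect on 28-day all-cause mortality will be assessed with a Cox proportional hazard model adjusted for baseline APACHE II score".
- Vital support-free days: "The effect on vital support-free days within 28 days will be assessed with a cumulative logistic model adjusted for the baseline APACHE II score".
- Length of stay: "will be estimated with generalized linear models adjusted for the APACHE II score using the distribution that best fits the data".

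The testing order comes from two sections. Statistical analysis principles makes the primary outcome the gate: "If the experimental group strategy is superior to the Control Group for the primary outcome (p value < 0.05), we will test the treatment effect". The Secondary outcomes list then sets the order as mortality, support-free days, length of stay.

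Table 1 records SOFA, lactate level, norepinephrine dose and invasive mechanical ventilation at randomisation. Heterogeneity of treatment effects uses SOFA, lactate and "invasive mechanical ventilation at inclusion" as subgroup factors. Baseline SOFA is a covariate only in the tertiary repeated-measures models.

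**The concern.** Mortality stands ahead of the other two secondary tests. If it misses p < 0.05, neither support-free days nor length of stay is formally tested, however clear their results. Power at that step therefore limits what the trial may formally conclude beyond its primary outcome.

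Support-free days has a further gap. It counts days free of cardiovascular, respiratory and renal support, yet the model takes no direct account of whether the patient was already ventilated, or on how much norepinephrine, at randomisation. For repeated SOFA the plan does adjust for the outcome's own baseline value.

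**Working it through.** **The plan's own figure.** The only stated power is 88% for the primary win ratio; none is given for the secondary models. A simulation with beta-binomial distributions matched to the stated means and SDs gave 98-99%, not 88%. The plan's own parameters and the dependence between components are not shown, so this does not prove 88% wrong, and nothing below rests on it.

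**Inputs (Sample size; Randomization).** 1,500 patients, 1:1, so 750 per arm; mortality 39% versus 33%; hospital stay among survivors 15.6 (SD 10.1) versus 14 (SD 9.9) days; two-sided alpha 0.05. No dropout is assumed.

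**Mortality, unadjusted.**
- Two proportions: null SE = √(2 × 0.36 × 0.64 / 750) = 0.02479; alternative SE = √((0.39 × 0.61 + 0.33 × 0.67) / 750) = 0.02474. Power = Φ((0.06 − 1.96 × 0.02479) / 0.02474) = Φ(0.46) = 67.8%.
- Schoenfeld: HR = ln 0.67 / ln 0.61 = 0.810; expected deaths = 0.36 × 1,500 = 540. Power = Φ(|ln 0.810| × √(540/4) − 1.96) = Φ(0.49) = 68.6%.

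**Length of stay, simple comparison of survivors.** Survivors: 750 × 0.61 ≈ 458 and 750 × 0.67 ≈ 503. SE = √(10.1²/458 + 9.9²/503) = 0.646; z = 1.6 / 0.646 = 2.47. Power = Φ(0.51) ≈ 70%.

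**Support-free days.** A rank comparison under the plan's own assumptions has about 98% power unadjusted.

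**Gain from more covariates, mortality.** The documents give no prognostic strengths, so these are assumed. Cox data were simulated with APACHE II and one further score that stands for what the four other variables add. Marginal mortality was held at 39% versus 33% (1,500 replications per row; Monte Carlo SE of each power about √(0.75 × 0.25 / 1,500) = 1.1 points).

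| Assumed c, APACHE II | Assumed c, all | Power % unadjusted | Power % APACHE II | Power % all | Gain over APACHE II (points) |
|---|---|---|---|---|---|
| 0.67 | 0.67 | 69.7 | 73.7 | 73.5 | about 0 |
| 0.66 | 0.71 | 67.9 | 72.1 | 75.4 | 3.3 |
| 0.65 | 0.74 | 69.2 | 73.2 | 81.4 | 8.2 |
| 0.65 | 0.78 | 70.4 | 73.3 | 84.9 | 11.6 |
| 0.72 | 0.75 | 68.5 | 77.5 | 80.8 | 3.3 |
| 0.71 | 0.78 | 70.5 | 76.9 | 83.9 | 7.0 |
| 0.70 | 0.80 | 70.1 | 75.3 | 87.2 | 11.9 |

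A separate logistic approximation, with c assumed to rise from about 0.67 to 0.70, 0.725 and 0.75, gave smaller gains: 71.7 to 73.4%, 71.5 to 74.4% and 72.4 to 77.5%, or 1.7, 2.9 and 5.1 points.

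**Where the gain comes from.** The Cox SE hardly moves: about 0.0865 unadjusted and 0.0866-0.0868 with all covariates. The estimate moves instead. In the last row the mean HR is 0.805 unadjusted, 0.791 with APACHE II and 0.763 with all.

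**Support-free days, smaller effect.** At an assumed marginal odds ratio of 1.3, the cumulative logistic model had 84-88% power with APACHE II alone and 87-94% with an informative further score: gains of about 1 to 10 points, and none if the score adds nothing (400 replications; Monte Carlo SE about √(0.85 × 0.15 / 400) = 1.8 points). The SE rose slightly here too, from 0.093-0.095 to 0.095-0.098.

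The gain for length of stay was not computed, because its distribution and link are left open.

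**The case against.** The case for leaving the plan alone is a fair one. One prespecified severity score gives a valid test in a randomised trial. APACHE II is used consistently: it stratifies the primary analysis, enters the imputation and defines the risk modelling. For mortality the plan cites the earlier trial as precedent. All of this stands, and it is why this is a recommendation and not a fault.

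Four stronger readings are tempting, and the documents do not support them:

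- **That the trial's gatekeeping test is weakened.** The gate to all secondary testing is the primary win ratio, which these models do not touch. Mortality gates only the two later secondary tests.
- **That precision is lost.** In the Cox and cumulative logistic models the standard error stays flat or rises slightly. Power rises because the conditional effect lies further from the null, so the estimand changes with it.
- **That mortality is clearly the weakest test.** Length of stay, at about 70%, is essentially level with mortality at 68%. It also adjusts for APACHE II alone, so it belongs in the fix.
- **That chance imbalance in ventilation threatens validity.** With 750 per arm the SE of the between-arm difference is at most √(2 × 0.25 / 750) = 2.6 points, and valid p values already allow for it.

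Two practical cautions also stand. Entry requires a vasopressor, not norepinephrine specifically, so the dose variable needs a coding rule. Five covariates without stated functional forms would open new choices in formally tested models.

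**Conclusion.** The point holds as an efficiency improvement. Baseline information that is already collected is left out of three formally tested models, and the first of these decides whether the other two are tested.

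Mortality power is about 68% unadjusted. With APACHE II alone it is 72-78% under assumed c-statistics of 0.65-0.72. Further covariates add about 0 to 12 points: nothing if they share all their information with APACHE II, and the top of the range only if the combined c-statistic reaches about 0.78-0.80. The range rests on those assumptions, on the plan's 39% versus 33%, and on no dropout.

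For support-free days the power gain is small under the plan's own effect sizes, and the main benefit is to account for the patient's support at randomisation. The 70% for length of stay is a rough comparison among survivors, not the planned model.

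**What to change.** Before database lock, amend Secondary outcome analysis so that all three models adjust for APACHE II, baseline SOFA, log lactate, norepinephrine dose and invasive ventilation at randomisation. State in the same place:

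- the functional form of each continuous covariate (for example linear, with lactate on the log scale);
- the coding of norepinephrine dose for patients on another vasopressor (for example 0);
- one simple rule for missing baseline values, such as the median over both arms combined.

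Keep the APACHE II-only models as supportive analyses, so that the results stay comparable with the earlier trial.

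The change costs SAP wording only and needs no new data. About 540 expected deaths easily carry four more covariates. The price is that the hazard and odds ratios are conditional on a larger covariate set, which the supportive models make visible.

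The tertiary free-days models ("Vasopressor support-free days, MV-free days, and RRT-free days will be assessed with a cumulative logistic model adjusted for the baseline APACHE II score") could also take each outcome's own baseline state. That is optional, since those results are exploratory and carry no p values.

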## Tertiary outcome analysis

All-cause mortality within 90 days will be assessed with a Cox proportional hazard model adjusted for the baseline APACHE II score. The effects on the length of hospital stay, length of ICU stay, time to cessation of vasopressor support, time to cessation of MV, and time to cessation of RRT will be estimated with generalized linear models using the distribution that best fits the data and adjusted for the baseline APACHE II score. Vasopressor support-free days, MV-free days, and RRT-free days will be assessed with a cumulative logistic model adjusted for the baseline APACHE II score.^15,16^Effects on repeated measures of organ dysfunction at 7 days (SOFA), CRT and lactate levels will be analyzed via mixed models with patients as random effects, treatment groups as fixed effects, and treatment‒time interactions while adjusting for the baseline SOFA score. The effect will be presented as the difference between the slopes of the groups or, equivalently, the treatment‒time interaction. The effects on other continuous outcomes, such as length of hospital stay and length of ICU stay, will be calculated with generalized linear models with the distribution that best fits the data. Adjustments for baseline APACHE II score, evolution volume resuscitation fluid, and net fluid balance will also be assessed with generalized linear models with the distribution that best fits the data and no adjustments for baseline covariates. For all continuous outcomes for which we will define the best distribution at the time of statistical analysis, the criteria will involve assessing which distribution best fits the data via residual and QQ-plot analysis, which will be published in the supplementary manuscript to increase transparency.

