## METHODS

### Trial design

ANDROMEDA-SHOCK-2 is a prospective, multicenter, parallel-group, randomized trial that compares a 6-hour protocol of hemodynamic phenotype-based, CRT-targeted resuscitation *versus* standard care resuscitation in patients with septic shock. The trial protocol (version 1.0 from September 2021) was published and is registered with ClinicalTrials.gov (NCT05057611). The study is being conducted in 81 intensive care units (ICUs) in Latin America, North America, Europe, and Asia. The study was approved by the Ethics Committees of all the participating institutions. The main study interventions are summarized in figure 1.

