### Randomization

Eligible patients are randomly allocated to the intervention (CRT-P) or control (standard care) groups. A randomization sequence with an allocation of 1:1 is generated by a computer program. Study group assignment is achieved by means of randomized permuted blocks of variable size with stratification by center. Allocation concealment is maintained by means of central randomization via the web via Castor EDC®.

Because this is a nonpharmacological intervention, blinding the medical team is not feasible.

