### Timing of outcome assessment

We will assess outcomes at 6, 24, 48, and 72 hours; during the first 7 days until ICU discharge; at 28 and 90 days; and at ICU and hospital discharge.

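### One slope difference for SOFA, CRT and lactate can carry the wrong sign if an early benefit fades; separately, centre, the randomisation stratum, is in no treatment-effect model

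*SAP article*

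**What the plan says.** **Repeated measures.** Under Tertiary outcome analysis, SOFA shares one model with the two perfusion markers: "CRT and lactate levels will be analyzed via mixed models with patients as random effects, treatment groups as fixed effects", plus a treatment-by-time interaction, "while adjusting for the baseline SOFA score". On the effect measure: "The effect will be presented as the difference between the slopes of the groups". The text adds that this is equivalent to the interaction.

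**Timing.** Trial design says the study "compares a 6-hour protocol of hemodynamic phenotype-based, CRT-targeted resuscitation" with standard care. Timing of outcome assessment says: "We will assess outcomes at 6, 24, 48, and 72 hours", followed by later time points. The dummy baseline table has rows for lactate level and for "Capillary refill time (seconds"), so both markers have a value at randomisation.

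**Centre.** Randomization uses "randomized permuted blocks of variable size with stratification by center". The win ratio is stratified by APACHE II. Mortality at 28 days uses a "Cox proportional hazard model adjusted for baseline APACHE II score". The other secondary models, and the tertiary survival, duration and free-day models, also adjust for APACHE II; fluid outcomes have no covariates. Site is used only when missing primary outcome data are imputed (Analysis populations).

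**Status.** Statistical analysis principles gives 95% intervals for all effects, gives no p values for tertiary outcomes and calls them exploratory.

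**The concern.** A slope difference equals the treatment-by-time interaction only when time is a single linear term, so the text commits to linear time. A 6-hour intervention aimed at CRT may well have its largest effect on CRT at the first visit. If control patients then catch up, they have further to fall and show the steeper decline. The planned summary would report this as a better course under control.

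CRT is the variable the strategy targets, so a wrong-signed estimate with an interval would mislead readers about whether the strategy did what it set out to do. The Harms section also relies on tertiary outcomes to reflect possible harm.

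The centre question is separate. When allocation is balanced within centre, an analysis that ignores centre leaves between-centre variation in the error term and gives up some power.

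**Working it through.** The plan gives no figure on this point. Its 88% power refers to the win ratio and is not used here. All CRT courses and intraclass correlations (ICCs) below are assumptions, because the document gives none.

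**1. Slope difference.** Assume CRT is measured at 6, 24, 48 and 72 h in all patients. In balanced data a random-intercept model gives a treatment-by-time estimate equal to the least-squares slope of the between-arm difference d(t):

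slope = Σ(t − t̄)·d(t) / Σ(t − t̄)², with t in days.

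*Four visits* (t = 0.25, 1, 2, 3; mean 1.5625). Deviations are -1.3125, -0.5625, 0.4375, 1.4375, with sum of squares 4.297. For d = -0.30, -0.15, -0.05, 0 the numerator is 0.3938 + 0.0844 − 0.0219 + 0 = 0.4563, so the slope is 0.4563/4.297 = **+0.106 s/day**. The average of the four differences is -0.50/4 = -0.125 s, a benefit.

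*Baseline as time 0* (mean 1.25). Deviations are -1.25, -1, -0.25, 0.75, 1.75, with sum of squares 6.25. With no difference at baseline the numerator is 0.30 + 0.0375 − 0.0375 + 0 = 0.30, so the slope is 0.30/6.25 = **+0.048 s/day**.

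The same formulas for other assumed courses (negative favours CRT-P):

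| Difference at 6, 24, 48, 72 h (s) | Four visits (s/day) | Baseline as time 0 (s/day) |
|---|---|---|
| -0.30, -0.15, -0.05, 0 | +0.106 | +0.048 |
| -1, -0.5, -0.2, 0 | +0.351 | +0.156 |
| -0.6, -0.5, -0.4, -0.3 (part fade) | +0.108 | -0.016 |
| -1 throughout (sustained) | 0.00 | -0.20 |
| -0.25, -0.5, -0.75, -1 (widening) | -0.27 | -0.31 |

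With baseline as time 0 and benefit sizes b, the sign is right when 0.75·b48 + 1.75·b72 exceeds b6 + 0.25·b24. A part fade keeps its sign only while enough benefit remains at the later visits.

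**2. Precision of the wrong-signed estimate.** Assume 750 patients per arm, a residual SD of 0.8 s and no random slope. Then SE = √(2 × 0.64 / (750 × 4.297)) = 0.020, and 0.106 ± 1.96 × 0.020 gives about 0.067 to 0.145. With baseline as time 0, SE = √(2 × 0.64 / (750 × 6.25)) = 0.0165, giving about 0.016 to 0.080. Both intervals exclude zero on the wrong side.

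**3. Role of the covariate.** A covariate that is constant over a patient's visits does not alter that patient's slope. In 300 simulated trials per setting (N = 1,500, SOFA–CRT correlation 0.3, within-patient correlation 0.5), the slope difference was +0.106 adjusting for SOFA and +0.107 adjusting for own baseline, with SE 0.0199 in both. What changed was the SE of the average post-baseline difference: 0.0445 against 0.0358, a reduction of 1 − 0.0358/0.0445 = 20%.

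**4. Centre.** Simulation with 81 centres, permuted blocks and 1,500 patients (continuous outcome, 1,000 trials per ICC):

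| Assumed ICC | Type I error, centre ignored | Power, ignored / adjusted |
|---|---|---|
| 0 | 0.046 | 0.869 / 0.868 |
| 0.02 | 0.050 | 0.893 / 0.894 |
| 0.05 | 0.048 | 0.899 / 0.913 |
| 0.10 | 0.042 | 0.881 / 0.896 |
| 0.20 | 0.024 | 0.905 / 0.934 |

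A second simulation, of mortality, compared an unadjusted test with a centre-stratified Cochran–Mantel–Haenszel test. Power was 66.9 against 67.7% at ICC 0.05, 61.5 against 63.9% at 0.10 and 57.8 against 62.5% at 0.18. The gains are 0.8, 2.4 and 4.7 points. In the same runs, ignoring centre overstated the SE of the log win ratio by about 1 to 6%.

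**The case against.** - **The reversal rests on an assumed course.** This stands. No CRT trajectory is given. A reader might infer that the slope will be wrong-signed; the document supports only that it can be. The table shows courses where the sign is right, and the plan does not say whether baseline enters as time 0.
- **The SOFA covariate.** A reader might infer that adjusting for SOFA produces the reversal, or that it widens the interval for the planned slope. Neither holds (step 3). Changing the covariate alone would leave the sign problem in place.
- **An early CRT analysis is already planned.** The section on preplanned post hoc analyses lists CRT kinetics during resuscitation, and supplementary tables not shown here may display values by visit. This softens the point. It does not replace the effect measure that Tertiary outcome analysis fixes for these outcomes.
- **The outcomes are exploratory and carry no p values.** True, and no trial conclusion rests on them. Intervals will still be shown and read.
- **Adjusting for APACHE II rather than 81 centres is defensible.** Largely true. APACHE II may absorb some between-centre case mix, and centres average only 1,500/81, about 18 patients. A reader might infer that omitting centre threatens validity or inflates false positives; step 4 shows the opposite. Nor would adding centre narrow intervals in the non-linear models. In a logistic check the SE of the log odds ratio rose from 0.109 to 0.112, 0.114 and 0.117 at ICC 0.05, 0.10 and 0.18, while the estimate moves away from the null. The gain there is power for a centre-conditional effect.

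**Conclusion.** The concern holds in a limited form. The planned effect measure for SOFA, CRT and lactate takes the wrong sign when the arms separate early and then converge fully. In the main illustration it reads +0.106 s/day (+0.048 with baseline as time 0) although CRT-P is never worse. A sustained benefit becomes invisible if baseline is not an outcome time. A widening benefit is reported with the right sign and, with baseline as time 0, so are a sustained benefit and one that fades only moderately. The cause is the single linear slope. These sizes rest on assumed CRT courses, complete data and measurement at the four early visits.

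Omitting centre is a missed, inexpensive gain: about 0 to 5 points of power over assumed ICCs of 0 to 0.20, with type I error at or below its nominal level. It is not a bias towards a false positive. Overall severity is minor to moderate.

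**What to change.** **Repeated measures.** For SOFA, CRT and lactate, fit visit as a category with visit-by-arm terms. Adjust each outcome for its own recorded baseline, which improves the precision of the visit-specific differences. Report the arm difference with its 95% interval at each visit, with 6 h first for CRT and lactate. The slope difference may stay as a supplement, provided the plan says whether baseline counts as an outcome time.

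**Centre.** Add centre as a random intercept or frailty, alongside APACHE II, in the secondary and tertiary models that use it. Keep the primary win ratio as planned and check its p value by re-randomisation within centre.

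**Cost.** Changes to the SAP wording before database lock, several visit estimates in place of one slope, slightly more complex models, and effects in the non-linear models that are conditional on centre. No new data are needed.
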